**INDEX OF ABBREVIATIONS AND ACRONYMS**

AAQoL- Quality of Life Questionnaire in Adults with ADHD;

ABENEPI- Brazilian Association of Neurology, Psychiatry and Allied Professions;

ADHD- Attention Deficit Disorder and Hyperactivity;

APB- Psychiatric Association of Bahia;

ASRS- Adult Self-Report Scale;

CPC-SSP- Research Center Clinical Sanatorium of São Paulo;

DSM-IV-TR- Diagnostic and Statistical Manual of Mental Disorders, Fourth Edition, Text Revision;

EEG- Electroencephalography;

ICF- Informed consent form;

mA- Miliampère;

MINI-plus- Mini International Neuropsychiatric Interview Plus;

MMSE- Mini-Mental State Examination;

QEEG- Quantitative electroencephalography;

SNB- Neurology Society of Bahia;

tDCS- Transcranial Direct Current Stimulation.

**I. OBJECTIVES**

I.a. General

To assess the neurobiological aspects associated with attention deficit-hyperactivity disorder (ADHD) and the contribution of transcranial direct current stimulation (tDCS) on inhibitory control.

I.b. Specific

I.b.1. To assess the contribution of transcranial direct current stimulation, comparing it to sham intervention, on the modulation of inhibitory control in adults with ADHD through Go/ No go task;

I.b.2. To examine the neurobiological aspects evidenced through the brain electrical activity observed by power analysis of frequency bands in patients with ADHD, using quantitative electroencephalography;

I.b.3. Proceed the Reconstruction of Functional Brain Network, of each participant, based on the quantitative EEG data through mathematical-computational modeling;

I.b.4. To register indicators of quality of life in adults with attention deficit-hyperactivity disorder through the Quality of Life Questionnaire for Adults with ADHD (AAQoL);

**II. THEORETICAL**

Human development includes differents stages of social and environmental exposure influenced by physiological and cultural aspects building the psychic and physical scope of an individual. In this context, attention deficit-hyperactivity disorder (ADHD) as a condition expressed by hyperactivity, impulsivity and reduced sustained attention, may contribute to the impairment of the social and emotional development of the individual, if there is no an early and effective intervention [1,2].

Attention deficit-hyperactivity disorder presents prevalence rates, in American studies, of 5 to 9% in childhood, especially in school age and between those, 67% still present the symptoms in adulthood, what may compromises the psychosocial, professional and emotional development [3- 6]. In a recent national study, Arruda et al observed a prevalence of ADHD among children and adolescents of 4.4% [7]. However, despite of the significant social impact, some of these patients remain undiagnosed and therefore without proper therapeutic intervention. The diagnosis is based on clinical assessment and identification of symptom established by the Diagnostic and Statistical Manual of Mental Disorders, Fourth Edition, Text Revision (DSM-IV-TR), as inattention, hyperactivity, impulsivity and general criteria [1 - 4, 6].

The clinical presentation possibly arises from disorders in the prefrontal cortex and its subcortical connections [1, 6, 8]. This assumption is supported by the hypothesis that it is a neurobiological disorder, evidenced by functional deficit in neurotransmitters such as dopamine and norepinephrine, and by disorders in the frontal lobe, triggering the symptoms observed in ADHD patients as impulsivity, difficulty to inhibit distractors behaviors, to plan and execute tasks under focused attention and to keep concentration [6]. These observations evidence the impairment of important executive functions in individuals with ADHD [2-4, 6, 8, 9].

Prefrontal cortex is the main brain area responsible for executive functions [10]. These functions correspond to neurocognitive skills of planning and execution of intentional and self-organized actions [8, 9, 11]. Considering these executive domains, inhibitory control is one of the most affected aspects in attention deficit-hyperactivity disorder [6]. It corresponds to the ability to inhibit inappropriate or inconvenient behavior and/ or inhibiting response to distractors stimuli [6, 8, 12]. A disorder of inhibitory control, thus significantly affects the social, emotional and cognitive performances of the individual, either by prevent the discontinuation of an inappropriate action or for not intervening in the interruption of a stimulus that discontinue appropriate responses [2, 3, 6].

There is evidence of a physiological association between the prefrontal cortex and inhibitory control [8, 12, 13]. Changes on this anatomical structure may account for an impairment in inhibitory control, evidenced behaviorally by actions that reflect inconsequence, unpredictability, intolerance to waiting, quick and inconsistent responses, possible exposure to hazards, and acceptance of multiple responsibilities and tasks simultaneously with consequent further withdrawals [8, 13].

This anatomical relationship and understanding of the neurobiological mechanisms comprises a physiological framework that supports the hypothesis that activation of the prefrontal area will result in a larger and more suitable inhibitory control, minimizing the socio-affective consequences associated to this condition.

Transcranial direct current stimulation is a simple and well known neuromodulatory technique [14, 15], that uses low voltage electrical currents to increase or decrease neuronal excitability of the stimulated area [14, 16]. This is a noninvasive and safe stimulation, having infrequent and mild adverse effects characterized by local discomfort, itching, paresthesia and/ or headache, with short lasting [16]. The application of this technique and the assessment of its effects will be performed by clinical observation considering as parameters a reducing on symptomatology evaluated through neuropsychological task- Go/ No go, and by neurophysiological assessments as quantitative electroencephalography (QEEG) and reconstruction of brain networks. In this trial, these techniques will assess possible prefrontal cortex activation after tDCS, and will evaluate the hypothesis of increase on inhibitory control and its behavioral consequences. It will be applied anodal stimulation at 1mA, aiming to enhance the excitability of the dorsolateral prefrontal cortex, according to the anatomical and physiological correlation mentioned above. At the end, it is expected a better adjustment of the behavioral responses associated to inhibitory control that compromise, ultimately, the quality of life of ADHD individuals [16].

The concept of quality of life is complex, wide and can be understood in different contexts: biological, economical, cultural and social [17]. Considering the approach of this study- the biological perspective, means quality of life as the condition of the individuals understand the disease, its challenges and behavioral inadequacies in a clear way that enables them to define adaptation strategies.

Regarding treatment approaches, there are pharmacological resources such as methylphenidate and lisdexamfetamine, that contribute to a better symptomatical control [18]. However, these drugs present important side effects, with unpredictable occurrence, such as insomnia, appetite loss, headache, muscle spasms, irritability, anxiety, cardiovascular events, among others, which may eventually result in discontinuation of the treatment [18- 22]. In this context, new therapeutic strategies with a simple and safe profile as transcranial direct current stimulation are essential.

The aim of this trial is to investigate the efficacy of tDCS over the prefrontal cortex on the modulation of inhibitory control in adults with ADHD, evidenced by behavioral and neurophysiological parameters previously mentioned. We expect to observe an increase of inhibitory response in ADHD individuals, that may result in a greater ability to inhibit inappropriate behaviors through the application of a low cost, safe and non-invasive technique.

**III. MATERIALS AND METHODS**

**III.a. Study Design**

This is a parallel and cross-sectional study which will include descriptive and analytical steps designed to investigate the neurobiological aspects of patients with attention deficit-hyperactivity disorder, and the response of these parameters, associated to inhibitory control, to the modulation by transcranial direct current stimulation.

**III.b. Population**

Patients with attention deficit hyperactivity disorder will be recruited by letter and email to the Psychiatric Association of Bahia (APB), Bahia Neurology Society (SNB) and the Brazilian Association of Neurology, Psychiatry and Allied Professions (ABENEPI) - chapter Bahia. We will also contact by mail and telephone, professional experts in ADHD, inviting them to refer potential patients for the study. We will also publish advertisements on the internet and on social networks, from October 2012 to December 2012, according to the inclusion criteria.

III.b.1. Inclusion criteria

-Ability to understand and sign the informed consent form;

-Diagnosis of attention deficit-hyperactivity disorder according to DSM-IV-TR and Adult Self-Report Scale (ASRS);

-Residents in Bahia;

-18 years old or older;

III.b.2. Exclusion criteria

-Major psychiatric disorders such as schizophrenia and bipolar disorder;

-Inability to understand the questionnaires applied (cognitive impairment- score ≤ 24 on the Mini-Mental State Examination) or illiterate;

-Abuse of psychoactive substances or alcohol, except nicotine and caffeine, during the last 12 months.

III.b.3. Sample size

This will be a randomized sample of ADHD individuals recruited through Internet media, social networks, and contact with ADHD experts and specialized societies of neurology, psychiatry and related fields, during the study period. A sample size of 50 subjects was calculated assuming a difference in proportion between the active tDCS and sham control groups of 40% on the Go/ No go performance, before and after interventions.

This calculation was performed using the statistical program STATA 12.0, considering an alpha of 0.05 and a power of 0.80, resulting in an sample of 25 subjects in each group, intervention and control. To address unexpected factors, we applied a drop-out rate of 20%, reaching a total sample size of 60 individuals.

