**III.c. Study Variables**

III.c.1. Dependent variables

The following variables will be evaluated: neuropsychological outcome (Go/ No tasks); power analysis of frequency bands through QEEG; and brain reconstruction network model of each individual by QEEG.

III.c.2. Independent variables

Transcranial direct current stimulation and sham procedure.

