**III.d. Procedures**

After screening through psychiatric interview, explanation about all steps of this study, and agreement expressed through signed informed consent form, ADHD patients will underwent a cognitive evaluation through the Mini-mental state examination (MMSE), Mini International Neuropsychiatric Interview Brazilian (MINI PLUS), Adult Self-Report Scale (ASRS), Quality Questionnaire life in Adults with ADHD (AAQoL), and an interview through a questionnaire. This evaluation script is an instrument based on the ADHD diagnostic criteria from DSM-IV-TR, and consists on epidemiological and clinical questions.

Individuals will be divided into two groups by block randomization, aiming at a balanced distribution between the groups (30 subjects each). Blocks shall be composed of 10 subjects, totaling six blocks. To compose each group will be called 5 individuals from each block.

Following it, the brain electrical activity will be recorded by EEG with 32 channels placed on the scalp acoording to the 10-20 EEG international system, during 5 minutes. The recording will be in a resting state, the first minute with eyes open looking for a fixed point, and the last 4 minutes with eyes closed. Then, participants will be asked to perform tasks on the computer: two Go / No go tasks adapted from the original version, the first using as a target a fruit and the second a letter. After the cognitive tasks, subjects will undergo active or sham stimulation, according to the previous randomization.

Participants of the intervention group will be submitted to tDCS at 1mA, anodal electrode over the left dorsolateral prefrontal cortex and cathodal electrode over the equivalent area on the right side. On control group subjects (sham group), electrodes will be placed at identical positions and sham stimulation will be applied. The stimulation device will turn on for only 30 seconds so that the patient will feel the initial sensation, then shutting down. The intervention and sham procedure will take place in one single session of 20 minutes to evaluate the immediate effect.

At the end of the intervention, subjects will perform again two Go/ No go tasks (randomly selected to avoid learning effect), and they will undergo another EEG recording, with the same previous technical caracteristics.

This study will be performed at Laboratory of Functional Electrostimulation at Federal University of Bahia.

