**III.e. Statistical Analysis**

**Step 1**: socio-demographic, clinical and epidemiological description of the groups, using the usual procedures of descriptive statistics such as calculation of frequencies, measures of central tendency and dispersion;

**Step 2**: characteristics will be compared between groups at the baseline, using one-way analysis of variance (ANOVA) for continuous variables and chi-square test for categorical variables;

**Step 3**: Shapiro-Wilk test will be performed to assess normality assumption of the outcome variables;

**Step 4**: analysis of paired and independent samples using the t-test for comparison within each group and between intervention groups, or applying equivalent non-parametrics tests (according to Shapiro-Wilk test results), before and after intervention;

**Step 5**: Person's chi-square to evaluate blinding effectiveness, comparing between groups.

These analysis will be performed through Stata, version 12.0 for Windows. Results will be considered statistically significant if p ≤ 0.05.

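### The 80% power and 25 per group are stated for a difference in proportions, but the protocol plans to test the outcomes by t-test or a rank equivalent and defines no Go/No-go responder

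*Protocol*

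**What the plan says.** Protocol III.b.3 (Sample size) states: "A sample size of 50 subjects was calculated assuming a difference in proportion between the active tDCS and sham control groups of 40" per cent in Go/No-go performance, before and after the interventions, "considering an alpha of 0.05 and a power of 0.80", "resulting in an sample of 25 subjects in each group, intervention and control". It then adds an allowance for losses: "we applied a drop-out rate of 20%, reaching a total sample size of 60 individuals". III.d (Procedures) allocates 30 to each group. The proportion expected under sham is not given. Nor is it stated whether the test is one- or two-sided, or whether a continuity correction was used.

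III.c.1 (Dependent variables) lists the outcomes as "neuropsychological outcome (Go/ No tasks); power analysis of frequency bands through QEEG", followed by the brain network model. The Go/No-go outcome has no cut-off, responder rule or binary form there, and none in the objectives or in III.d.

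III.e (Statistical Analysis) has five steps. Step 3 checks the outcome variables for normality. Step 4 analyses paired and independent samples "using the t-test for comparison within each group and between intervention groups", or uses non-parametric equivalents. Chi-square appears only in Step 2, for categorical baseline characteristics, and in Step 5, for blinding.

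**The concern.** A power figure describes one test, on one variable, under one assumed effect. Here the sample-size section describes a comparison of two proportions, and the analysis section describes a comparison of two sets of scores. The inputs differ: a test of proportions needs the two proportions, while a t-test needs a mean difference and an SD. The protocol gives neither the control proportion nor any mean or SD.

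At stake is how the result can be read. The 80% is the only power claim in the document, and Go/No-go is the only outcome it cites. Whoever interprets the between-group comparison, especially if it is not significant, has no statement of the effect that the comparison could detect. A statistical analysis plan could add detail, but the sample-size basis and the outcome test are both already fixed in the protocol, and they disagree.

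**Working it through.** **1. Reproducing 25 per group.** Inputs from III.b.3: difference 0.40, alpha 0.05, power 0.80, equal groups. Assumed here: a two-sided test (z = 1.960 and 0.842) and a range of control proportions, since none is stated. With p1 and p2 the two proportions, p their mean and D = p2 − p1:

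n = [1.960·√(2p(1−p)) + 0.842·√(p1(1−p1) + p2(1−p2))]² / D²

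With continuity correction: n_c = (n/4)·[1 + √(1 + 4/(nD))]²

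- 10% versus 50%: √0.42 = 0.648 and √0.34 = 0.583, so n = (1.270 + 0.491)²/0.16 = 19.4. Corrected: (19.4/4)·(1 + √1.516)² = 24.1, rounded up to **25**.
- 30% versus 70%: n = (1.386 + 0.545)²/0.16 = 23.3, rounded up to 24. Corrected: 28.1, rounded up to 29.

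| Control vs active (assumed) | n per group, uncorrected | n per group, corrected |
|---|---|---|
| 10% vs 50% | 20 | 25 |
| 15% vs 55% | 22 | 26 |
| 20% vs 60% | 23 | 28 |
| 30% vs 70% | 24 | 29 |
| 40% vs 80% | 23 | 28 |
| 50% vs 90% | 20 | 25 |

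So 25 is reachable with a two-proportion formula. It cannot be confirmed from the text, because it depends on the missing control proportion and on the choice of formula. At 25 per group, the power of such a test runs from 74% (30% vs 70%, corrected) to 93% (5% vs 45%, uncorrected) over assumed control proportions of 5% to 50%.

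**2. Evaluable number.** 50 × 1.2 = 60 randomised, 30 per group. A 20% loss leaves 30 × 0.8 = 24 per group, one below the 25 calculated.

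**3. Power of the planned test.** For a two-sided independent t-test with n per group, the statistic has 2n − 2 degrees of freedom and noncentrality d·√(n/2). Here d is the difference in SD units of whatever score is compared. At n = 25 there are 48 degrees of freedom and the critical value is 2.011. Since the protocol gives no mean difference or SD, d is an assumed range:

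| d (assumed) | Power, 25 per group | Power, 30 per group |
|---|---|---|
| 0.3 | 18% | 21% |
| 0.5 | 41% | 48% |
| 0.6 | 55% | 63% |
| 0.8 | 79% | 86% |
| 1.0 | 93% | 97% |

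Solving for 80% power gives d = 0.83 at 24 per group, 0.81 at 25 and 0.74 at 30.

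**4. The scale of d.** Step 4 does not say whether post-intervention scores or changes are compared between groups. If changes are compared, d is in units of the SD of change, which is √(2(1 − r)) times the raw SD when the SD is equal before and after. With an assumed pre–post correlation r = 0.7, that factor is √0.6 = 0.775, and d = 0.81 corresponds to 0.81 × 0.775 = 0.63 raw SD.

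**The case against.** The best defence is that nothing is miscalculated and that the trial may be well powered. Both parts stand. The 25 can be reproduced, and the t-test has 80% power or more at 25 per group if the true standardised difference is at least 0.81. A reader might infer from the 41% at d = 0.5 that the trial is underpowered, or from the 74% that even the proportion calculation falls short. The documents support neither inference. No effect on the score scale is stated, so no value of d is favoured. The 74% is the lowest corner of the 74% to 93% range; the same 30% versus 70% gives 83% without the correction. Nor can one say that only a very large effect is detectable, since that depends on the scale, as the 0.63 raw SD example shows.

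A second defence is that the 40% may mean each subject's share of correct responses, or a relative change, rather than a proportion of responders. The wording is ambiguous. A share of correct responses would suit a t-test. But it is a continuous score for each subject, its power depends on the between-subject SD, and the two-proportion basis still does not apply.

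A third is that Step 4 also allows non-parametric tests. Rank tests compare scores, not proportions of responders, so the mismatch remains.

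**Conclusion.** The point holds as an inconsistency between design and analysis, not as an arithmetic error. The protocol's 80% belongs to a comparison of proportions that it does not plan, on a binary outcome that it does not define. The power of the planned comparison cannot be determined from the document and could lie on either side of 80%.

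That mismatch rests on the text alone. The power figures rest on two-sided alpha 0.05, equal groups, approximate normality of the score and assumed values of d; the reproduction of 25 rests on an assumed control proportion and formula. This should be fixed, but it does not put the number randomised in question by itself.

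**What to change.** Keep 60 randomised and make III.b.3 and III.e agree.

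Preferred: replace the proportion-based power statement with one for the planned test, for example: *With 24 evaluable per group (30 randomised, 20% dropout) and two-sided alpha 0.05, the between-group t-test on the Go/No-go score has 80% power for a standardised difference of 0.83 (0.81 with 25 per group).* Name the score and say whether it is the post-intervention value or the change. Add a sentence on why a difference of that size is plausible or relevant, because a detectable difference derived from a fixed number does not justify that number. Quote a figure for a baseline-adjusted comparison only if such an analysis is added to Step 4; otherwise the same mismatch returns.

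Alternative: define a Go/No-go responder, state the expected control proportion, sidedness and formula, and add a test of proportions for that outcome to III.e.

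Cost: one paragraph for the first repair, and an outcome definition and an analysis step as well for the second. Neither needs more patients. The restated figure may look less favourable than the present 80%.

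### The total of 60 does not cover the 20% drop-out it is said to allow for: 20% loss leaves 48 evaluable subjects, not the required 50

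*Protocol*

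**What the plan says.** The sample-size paragraph (protocol, III.b.3, within III.b. Population) works from a difference of 40% in proportions between active and sham stimulation on the Go/No go task, "considering an alpha of 0.05 and a power of 0.80". It reports that "A sample size of 50 subjects was calculated", "resulting in an sample of 25 subjects in each group, intervention and control". For losses it adds that "we applied a drop-out rate of 20%, reaching a total sample size of 60 individuals".

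Section III.d. Procedures carries the total forward as 30 subjects per group: "Blocks shall be composed of 10 subjects, totaling six blocks". The same section describes one stimulation session of 20 minutes, with the Go/No go tasks and EEG recorded before and after it. The protocol gives no other drop-out figure and no other rule for inflating the sample.

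**The concern.** Three numbers stand together in one paragraph: a requirement of 50, a drop-out rate of 20% and a total of 60. They cannot all hold. If one in five of the 60 is lost, fewer than 50 remain.

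The slip is a common one. The percentage is added to the required number when it should be taken off the enrolled number. As a result the trial falls below its stated minimum at exactly the loss rate it plans for, and the protocol claims a tolerance to attrition that it does not have. The sample-size statement would normally be repeated in the thesis and papers that section VII foresees, so the claim would be repeated with it.

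**Working it through.** **Inputs (protocol, III.b.3 and III.d)**

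- Required evaluable: N = 50, n = 25 per group
- Drop-out rate: d = 0.20
- Stated total: 60, as 30 per group in six blocks of 10
- Difference in proportions 0.40, alpha 0.05, power 0.80. The two proportions and the sidedness are not stated.

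**1. Reproducing the stated total**

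N x (1 + d) = 50 x 1.20 = 60. This gives the protocol's figure exactly.

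**2. The inflation that matches a drop-out rate**

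N/(1 - d) = 50/0.80 = 62.5, so 63. With equal groups, 25/0.80 = 31.25, so 32 per group and 64 in total.

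**3. What 60 delivers**

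- Remaining after 20% loss: 60 x 0.80 = 48, or 30 x 0.80 = 24 per group. The shortfall is 2 in total, 1 per group.
- Largest loss that leaves 50: 1 - 50/60 = 0.167, that is 10 subjects. To keep 25 in each group, no more than 5 of the 30 in either group may be lost.

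**4. Effect on power**

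Assumptions: two-sided alpha 0.05, a difference of 0.40, and a normal approximation with pooled variance under the null. The lower proportion p1 is varied because the protocol does not give it. With p2 = p1 + 0.40 and p the mean of the two:

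power = Φ{[0.40√n - 1.96√(2p(1 - p))] / √[p1(1 - p1) + p2(1 - p2)]}

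For the continuity-corrected version, n is replaced by n - 2/0.40 + 1/(0.40² n). This gives 20.25 for n = 25 and 19.26 for n = 24.

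Worked example, 0.10 vs 0.50, continuity-corrected. This pair (or its mirror image, 0.50 vs 0.90) gives a requirement of 24.12, rounded up to the protocol's 25 per group.

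- n = 25: (0.40 x 4.500 - 1.96 x 0.648)/0.583 = 0.909, power 0.818
- n = 24: (0.40 x 4.389 - 1.96 x 0.648)/0.583 = 0.832, power 0.797

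Range over the assumed proportions (pairs above 0.30 vs 0.70 mirror those below it):

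| Proportions | No correction, 25 → 24 | Continuity-corrected, 25 → 24 |
| --- | --- | --- |
| 0.05 vs 0.45 | 0.930 → 0.919 | 0.865 → 0.847 |
| 0.10 vs 0.50 | 0.895 → 0.882 | 0.818 → 0.797 |
| 0.20 vs 0.60 | 0.845 → 0.829 | 0.758 → 0.735 |
| 0.30 vs 0.70 | 0.828 → 0.812 | 0.739 → 0.716 |

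One subject fewer per group costs about 1 to 1.6 points without the correction and about 1.9 to 2.3 points with it.

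**The case against.** The best defence is that the 20% was meant as a margin on the calculated 50, against unforeseen events. Nowhere does the text say in so many words that 50 will remain after a fifth of the enrolled are lost. Read that way, 60 is consistent, and III.d uses it consistently. This explains how the figure arose, but it does not fit the words. The protocol calls the 20% a drop-out rate, which means a share of those enrolled, and on that meaning the requirement is missed.

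The points about weight do stand. The shortfall is one subject per group, and it appears only if losses exceed 16.7%. With a single session and no follow-up visit described, that is not the likely case, although unusable recordings or absences after randomisation are possible and the protocol offers no attrition data. Without a continuity correction, power stays above 0.80 at 24 per group for every pair tried. With the correction, several pairs are already below 0.80 at 25 per group, so the unstated proportions matter more for power than the drop-out formula does.

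**Conclusion.** The error is certain and its effect is small. The total of 60 comes from 50 x 1.2. It leaves 48 evaluable at the stated 20% loss, and it protects the requirement of 50 only up to 16.7%. This rests on the protocol's own three figures and needs no further assumption.

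The power cost of about 1 to 2.3 percentage points does rest on assumptions: a two-sided test, a normal approximation and a range of proportions that the protocol does not fix. The figures of 0.818 and 0.797 belong to one scenario that reproduces 25 per group. Nothing here threatens the trial's conclusions, but the sample-size statement is wrong as written and should be corrected.

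**What to change.** Replace the drop-out sentence in III.b.3 with one that states what 60 provides, for example:

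> *We will enrol 60 individuals (30 per group). This keeps 50 evaluable subjects, 25 per group if losses are equal, with drop-out of up to 16.7% (10 subjects).*

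The cost is one sentence and a slightly less favourable stated tolerance. The sample size, the 1:1 allocation, the six blocks of 10 and the analysis do not change, and for a single-session design this tolerance looks adequate.

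Keeping 20% as the planning rate would instead require 64 subjects for equal groups. That does not divide into blocks of 10, so the randomisation scheme in III.d would also have to change. The size of the shortfall does not call for this.
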